### Eligibility criteria

We will include women aged ≥ 18 and ≤ 60 years, with VL complaints assessed by direct question (yes / no) and by the VLQ [2] (very loose, moderately loose, slightly loose), and willing to attend treatments on the scheduled date and places.

Participants who present the following conditions will be excluded from the study: use of a pacemaker; decompensated heart disease; cognitive deficit; peripheral or central neurological disorders; the presence of any type of cancer; the presence of cervical dysplasia; history of active urinary or vaginal infection; decompensated metabolic diseases; patients undergoing physical therapy for pelvic floor disorders; patients using vaginal estrogen in the last 6 months; patients already undergoing surgery for prolapse or urinary or anal incontinence; patients with stage 2 POP onwards; force of contraction of the pelvic floor muscles equal to zero according to the modified Oxford scale [35].

### Recruitment

Women will be recruited from the Urogynecology outpatient clinic (CAISM / UNICAMP) and by social media advertisements, publicity posters, and printed ads from this study. All patients will be contacted by telephone by the researcher who applies the eligibility criteria and sends the VLQ via email or virtual communication platforms. The recruited participants will have their names, contact numbers, and VLQ responses recorded in a spreadsheet. A contact telephone with a virtual communication platform specific to this study is available for participants to contact the researchers whenever necessary. Participants will later be called by phone for the initial assessment. Participants interested in the study who did not pass the eligibility criteria are referred to the Urogynecology outpatient clinic for follow-up.

### Allocation

The randomization sequence will be carried out through a computer program, in a 1:1 allocation ratio, in two blocks. The numbers corresponding to the study groups (1. Radiofrequency and 2. Pelvic Floor Muscle Training) will be placed in opaque sealed envelopes that will be opened by the study participants after signing the consent form and undergoing initial assessment in the first clinical visit.

The researchers who will assist in completing the questionnaires and physical examination, the researchers responsible for ultrasound and the data analysts will be blinded for the treatment group to which the participants were randomized to.

### Initial assessment (first clinical visit)

Patients registered on the recruitment spreadsheet will be contacted by phone and the initial evaluation will be scheduled. In the initial evaluation, the participants will go through a lecture given by the researcher ([name]) in order to present the study, the assessments, the interventions, and the follow-up periods. At this point, the participants will be able to have all questions answered about the study. Participants who agree to participate in the study will receive a consent form for reading and signing. Participants will have their personal details protected and a number will substitute their identities.

### Interventions

The intervention period for both groups will be 12 weeks.

#### 1- Radiofrequency

The RF group will receive three radio frequency applications at 4-week intervals, (an initial application, a second application after four weeks, and a third application also after four weeks) comprising 12 weeks of intervention. The four-week period between applications will allow adequate healing of the vaginal tissues submitted to the application of radiofrequency. The procedure will be performed by a trained researcher ([name]) with a supervision of an experienced urogynecologist ([name]/[name]).

The Wavetronic 6000 Touch device with the Megapulse HF FRAXX system (Loktal Medical Electronics, São Paulo, Brazil) will be used, equipped with an electronic energy fractionation circuit, connected to a vaginal electrode with 64 microneedles 200μ in diameter and 1mm in length, and divided into an array of eight columns, with eight needles each. When pressing the trigger pedal, these 64 needles are not energized simultaneously and the energy release is randomized in columns of eight needles in a predefined sequence, which does not allow two adjacent columns to fire in sequence, preventing the thermal sum of the columns (control fractional firing system (*Smart Shoot*). This allows for cooling between the points and the preservation of tissues adjacent to the vaporized points, so that neocolagenesis and neoelastogenesis can occur, through fibroblastic stimulation [24].

*1*.*1-Procedure*. Topical anesthesia in the posterior vestibule and vaginal opening (mucosa) with 2% lidocaine gel, 2 to 3 minutes before the procedure (Table 1). A patient in a lithotomy position, with the lower limbs flexed and supported, will be introduced a disposable (high-impact polystyrene) vaginal speculum. A careful vaginal examination will be performed for any changes in the vaginal wall. Whiff test will be performed using a swab to collect vaginal discharge. A drop of 10% potassium hydroxide will be added over the vaginal secretion [36]. If a characteristic fishy odor is felt, the patient will not undergo RF and will be referred for evaluation of possible vaginosis. If the vaginal wall is intact and the whiff test is negative, the procedure will be continued, starting with topical anesthesia of the vaginal walls with 10% lidocaine spray. After 2 minutes, vaginal antisepsis with 2% aqueous chlorhexidine and cleaning with sterile 0.9% saline will be performed. After cleaning, the entire liquid content of the serum will be wiped with sterile gauze before starting to apply the RF.

**Table 1 pone.0259650.t001:** Pelvic floor muscle training and radiofrequency sessions according to the treatment duration.

Period	Interventions			
	Radiofrequency	Pelvic Floor Muscle Training		
**1 to 4 weeks**	1^st^ application	1^st^ phase	2^nd^ phase	3^rd^ phase
	• 2% Lidocaine Gel • Vaginal Examination with speculum • Whiff Test • 10% lidocaine spray • Cleaning: 2% aqueous chlorhexidine and sterile 0.9% saline • RF: 45Watts, Low Energy program (40 milliseconds) • Post-procedure orientation: 10-day sexual abstinence	• PFM maximum contraction (6 r / sustained 6 s/ 6 s rest: 1 time). Supine position. • PFM maximal contraction + transverse contraction (6 r / sustained 6 s/ 6 s rest: 1 time). Supine position. • PFM maximal contraction + hip elevation (6 r / sustained 6 s/ 6 s rest: 1 time). Supine position.	• PFM maximum contraction (1 cough / 3 r). Supine position. • PFM maximal contraction with the lower limbs extended and abducted (6 r / sustained 6 s/ 6 s rest: 2 times). Supine position. • PFM contraction in three stages—mild, moderate, maximum (6 r: 2 times). Sitting position. • PFM maximal contraction (6 r / sustained 6 s/ 6 s rest: 2 times). Standing position.	• Pelvic mobilization (anterior and posterior tilts, lateral tilts and rotation of the pelvis). Standing position. No PFM contraction in this phase. 10 repetitions each pelvic movement.
**5 to 8 weeks**	2^nd^ application	• PFM maximum contraction (6 r / sustained 8 s/ 8 s rest: 1 time). Supine position. • PFM maximal contraction + transverse contraction (6 r / sustained 8 s/ 8 s rest: 1 time). Supine position. • PFM maximal contraction + hip elevation (6 r / sustained 8 s/ 8 s rest: 1 time). Supine position.	• PFM maximum contraction (2 cough / 3 r). Supine position. • Fast PFM maximal (8 r: 2 time). Supine position. • PFM contraction in six stages—mild, moderate, maximum–maximum, moderate, mild (8 r: 2 times). Sitting position. • PFM maximal contraction (8 r /sustained 8 s/ 8 s rest: 2 times). Standing position. • PFM maximal contraction (8 r /sustained 8 s/ 8 s rest: 2 times). Four supports (hands and knees).	• Same Intervention (above)
	Same procedure (above)			
**9 to 12 weeks**	3^rd^ application	• PFM maximum contraction (6 r / sustained 10 s: 1 time). Supine position. • PFM maximal contraction + transverse contraction (6 r / sustained 10 s/ 10 s rest: 1 time). Supine position. • PFM maximal contraction + hip elevation (6 r / sustained 10 s/10 s rest: 1 time). Supine position.	• PFM maximum contraction (3 cough / 3 r). Supine position. • Fast PFM maximal (10 r: 2 time). Sitting position. • PFM contraction in six stages—mild, moderate, maximum–maximum, moderate, mild (10 r: 2 times). Sitting position. • PFM maximal contraction (10 r /sustained 10 s/10 s rest: 2 times). Standing position. • PFM maximal contraction (10 r /sustained 10 s/10 s rest: 2 times). Four to two supports (right hand and left knee/ left hand and right knee).	• Same Intervention (above)
	Same procedure (above)			

The device will be calibrated in FRAXX mode, 45 Watts, Low (initial application) and Medium (second and third application) Energy program (40 and 60 milliseconds, respectively), and the fractional vaginal electrode will be used. Applications will be under direct view. The electrode will be lightly pressed against the mucosa, without pressing, so that all microneedles are in uniform contact with the tissue. The application will be carried out sequentially on the lateral vaginal walls, in rows, avoiding overlapping, starting from the proximal third of the vagina to the distal third in the vestibule exposed by the opening of the speculum. The speculum will be gently rotated to the anteroposterior position for the application of the anterior and posterior vaginal walls. At the end of the procedure, the speculum will be gently removed. Patients will be advised on post-treatment care and the use of 5% dexpanthenol cream in the vaginal opening is recommended two to three times daily if there is any discomfort in the region for 2 to 3 days and interrupt sexual intercourse for 10 days. Patients will be instructed to contact the researchers if they experience any discomfort or notice any changes in vaginal discharge. These patients will be evaluated by an experienced gynecologist. There will be three vaginal applications at 4-week intervals, totaling 12 weeks of treatment.

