To our knowledge, to date, no clinical trial has been developed to assess the role of pelvic floor muscle and radiofrequency training in VL. Thus, the general objective will be to compare the effect of RF and PFMT in women with VL symptoms. The specific objectives are related to the assessment of the sexual function, vaginal symptoms, and sexual distress, as well as, to assess the impact of UI on patients’ quality of life. The POP staging, contractility, and pelvic floor muscle function will be also evaluated. Finally, we will assess the impression of improvement in VL complaints after the interventions.

Our hypothesis is that RF will be different from PFMT in treating women with VL symptoms.

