#### 2- Pelvic floor muscle training

The patients in the PFMT group will be assisted during the sessions by an experienced physiotherapist ([name]). The participants of this group will have 12 individual sessions of supervised PFMT, lasting 40–60 minutes, once a week, and totaling 12 weeks of treatment and continue their treatment with home PFMT program. To follow the treatment at home, patients will receive a printed diary containing the complete PFMT program, with figures illustrating the positions and orientations for each exercise for the pelvic floor muscles. Patients will have the possibility to contact the physiotherapist for questions regarding home treatment by video call, audio call or messages through a telephone number made available exclusively for the study. Patients will be instructed not to perform other exercises for the pelvic floor, different from the exercises proposed by the intervention program of the present study. Our intervention program for PFMT is based on the studies of Bo *et al*. [37] and Dumoulin *et al*. [38].

*2*.*1- Procedure*. The first PFMT session is longer and focused on the careful evaluation of the pelvic floor muscles in order to identify any muscle condition that interferes with the progress of the intervention; guidance on the correct performance of the pelvic floor muscle contraction with the aid of vaginal palpation and educational material; presentation of the PFMT program; and finally, the first sequence of exercises.

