Patients will be instructed to perform three phases of exercise in each session, with at least two sessions of the PFMT program per day (Table 1). The exercises will undergo progression every 4 weeks of intervention, totaling three progressions (6 repetitions, sustained for 6 seconds, 6 seconds for rest, 8 repetitions, sustained for 8 seconds, 8 seconds for rest, and 10 repetitions, sustained for 10 seconds, 10 seconds for rest). The first phase comprises three exercises of maximum contraction of the pelvic floor muscles in the supine position, with the lower limbs semiflected and the feet supported, associated with contraction transverse exercise, and hip elevation. The second phase comprises pre-contraction of the pelvic floor muscles associated with cough; maximum sustained contraction in the supine position with the lower limbs extended and abducted; fast contractions in both supine and sitting positions, contraction in three stages (mild, moderate, maximum) in a sitting posture; maximum sustained contraction in standing posture and four supports (hands and knees). The third phase comprises the relaxation period with breathing exercises associated with pelvic mobilization in a standing posture. No pelvic floor muscles contraction in this phase. Patients will be instructed on the importance of adhering to the PFMT. In case of two absences, the patients will be contacted and their permanence in the study will be reassessed.

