### Harms

The suspension of the intervention will occur through the verification of significant levels of discomfort during the application of vaginal RF (Visual Analogue Scale), as well as the significant occurrence of events such as urinary tract infection, vulvovaginitis, irritation and vaginal injury after application of vaginal RF (telephone contact). In these cases, an appropriate medical treatment will be offered. Women will be discontinued if they miss any radiofrequency sessions or if their presence in physiotherapy sessions does not reach 80%.

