### Data analysis

Initially, a descriptive analysis of the data will be performed to characterize the research participants, in the form of values ​​of absolute frequency and percentage (relative) for categorical variables and values of mean and standard deviation for numerical variables.

Statistical analysis of comparison and correlation of the obtained data will be performed. The Kolmogorov-Smirnov test will be performed to analyze the sample’s normality. Depending on the results obtained in the normality test, the Analysis of Variance (data with normal distribution) or Wilcoxon and Mann-Whitney Test (non-parametric data) will be used for comparative analyzes between the groups. Likewise, Pearson or Spearman tests will be used for correlational analyzes. Categorical variables will be analyzed using the chi-square test or Fisher’s exact test. Statistical analyzes will be performed using the statistical program SAS System for Windows (Statistical Analysis System), version 9.4, adopting a significance level of 5% (p <0.05). Study endpoints will be analyzed primarily for the per protocol population, and repeated, for sensitivity reasons, for intention-to-treat population [54].

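### Per protocol is the primary population for a difference hypothesis, although treatment can be stopped or withheld after allocation on grounds that differ by arm

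*Protocol article*

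**What the plan says.** The Introduction sets a difference hypothesis: "Our hypothesis is that RF will be different from PFMT in treating women with VL symptoms". The Sample size section matches it, with a two-tailed test at 0.05 and 80% power.

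On the analysis population, the Data analysis section states: "Study endpoints will be analyzed primarily for the per protocol population, and repeated, for sensitivity reasons, for intention-to-treat population".

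Under Allocation, the envelope is "opened by the study participants after signing the consent form and undergoing initial assessment in the first clinical visit". Everything below therefore happens once the arm is known to the participant:

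- **Attendance (Harms):** "Women will be discontinued if they miss any radiofrequency sessions or if their presence in physiotherapy sessions does not reach 80" per cent. For PFMT, section 2.1 adds: "In case of two absences, the patients will be contacted and their permanence in the study will be reassessed".
- **RF tolerability (Harms):** the intervention is suspended for marked discomfort while RF is applied, or for urinary infection, vulvovaginitis, irritation or vaginal injury afterwards. No PFMT counterpart is given.
- **Whiff test (section 1.1, RF procedure):** "If a characteristic fishy odor is felt, the patient will not undergo RF and will be referred for evaluation of possible vaginosis". Table 1 lists the test at the first application and refers the second and third back to the same procedure.
- **PFMT first session (section 2.1):** the muscles are evaluated "in order to identify any muscle condition that interferes with the progress of the intervention", but no withholding of treatment is attached to this check.

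**The concern.** When the question is whether two treatments differ, the comparison that carries the conclusion should keep the groups as randomised. A per-protocol set keeps only women who got through treatment under the rules. Here those rules ask different things of the two arms, so the women who remain need not be comparable, even though they were when the envelopes were opened. The authors themselves expect adherence to differ: the Trial design section says that RF is probably less exposed to adherence problems than PFMT.

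At stake is which result leads. If the two analyses disagree, the stated plan gives precedence to the one open to selection.

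**Working it through.** **1. Hypothesis against population.** The hypothesis is a difference, the sizing is two-tailed on an FSFI gain of 7 against 3 points, and no equivalence or non-inferiority margin appears. Nothing in the design calls for per protocol to lead.

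**2. Attendance rule.** PFMT has 12 sessions: 0.80 x 12 = 9.6, so 10 must be attended. Two absences prompt a reassessment and a third (9/12 = 75%) discontinues. For RF, "The RF group will receive three radio frequency applications at 4-week intervals"; one miss leaves 2/3 = 67%, also below 80%. The proportions are therefore consistent. What differs is the behaviour selected on: keeping three procedure visits, against keeping up weekly sessions for 12 weeks.

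**3. Tolerability.** The listed reasons for suspension can arise only from RF. Women who tolerate RF badly may plausibly also report less improvement, but the article gives no rates.

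**4. Whiff test.** This route operates only if a withheld application is treated as missed and discontinued women are left out. Inputs: 34 women per arm (Sample size); three applications; positivity p per application, which is not in the article and is assumed here, independent across applications.

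P(at least one positive in three) = 1 - (1 - p)^3

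| Assumed p | At least one positive | Expected of 34 |
|---|---|---|
| 1% | 3.0% | 1.0 |
| 2% | 5.9% | 2.0 |
| 5% | 14.3% | 4.8 |
| 10% | 27.1% | 9.2 |

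Reduce the primary outcome to improved or not, for illustration, and let the removed women's improvement rate differ from that of the others by 20 points (assumed). The shift in the RF rate is the share removed times that gap:

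- 1 woman: 1/34 x 20 = 0.6 points
- 5 women: 5/34 x 20 = 2.9 points
- at p = 10%: 0.271 x 20 = 5.4 points
- if every withheld application is deferred: 0

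The sign can go either way. The eligibility criteria exclude active vaginal infection, which should lower positivity at the first application.

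**5. Yardstick.** The standard error of the difference at a 50% rate is sqrt(2 x 0.25/34) = 12.1 points with 34 per arm, and sqrt(2 x 0.25/26) = 13.9 points with 26.

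**6. All routes together.** The 30% loss allowance covers 34 - 34/1.3 = 7.8 to 34 x 0.30 = 10.2 women per arm. If 8 to 10 women left one arm selectively with the same 20-point gap, its rate would move 8/34 x 20 = 4.7 to 10/34 x 20 = 5.9 points. If both arms lost 10 with gaps in opposite directions, the difference would move 2 x 5.9 = 11.8 points; with gaps in the same direction the shifts would cancel. These are outer illustrations, since the allowance also covers ordinary drop-out.

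**7. The planned 34 per arm.** It cannot be reproduced exactly because no standard deviation is given. 26 x 1.30 = 33.8 fits a standard deviation of about 5.1. Nothing here depends on it.

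**The case against.** A reader might infer that the whiff test removes RF women from the primary analysis. The text does not say so. The Harms rule is worded in terms of attendance, and a woman who comes, is examined and is referred has not plainly missed a session. Rescheduling rules and the exact per-protocol definition are details that an article may leave to the full protocol or analysis plan, so their absence is no fault. This objection stands, and it is why the whiff test is only one possible route. The check itself is sound clinical practice.

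A reader might also infer that RF is held to a stricter attendance standard. It is not: one miss in three already falls below 80%.

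It can be said that per protocol suits an equivalence question, and the Discussion does mention the therapies proving equally effective. But no margin is set and the stated hypothesis is a difference.

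Finally, intention-to-treat is already planned, so a disagreement would be visible. That is true, but it is ranked second. Nor is it proof against selection by itself: the article does not say whether discontinued women are still assessed, and the PFMT section speaks of reassessing whether a woman stays in the study. If their outcomes are not collected, the intention-to-treat repeat lacks them too.

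**Conclusion.** The point holds for the choice of primary population. A per-protocol lead does not fit a difference hypothesis when the grounds for stopping treatment differ by arm, and this is so without the whiff test. The conclusion assumes only that women whose treatment is discontinued fall outside the per-protocol set, as is usual.

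The size and direction of any bias cannot be derived from the article. On the assumptions shown, the whiff-test route is worth 0 to about 3 points of improvement rate for up to 5 women removed, against a standard error of 12 to 14 points, so it is probably modest. All routes together could matter more, but only under the outer assumptions in the working. The change is worth making before analysis; nothing here shows that a result would be wrong.

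**What to change.** 1. **Data analysis:** make intention-to-treat the main analysis for the RF versus PFMT conclusion, and per protocol the sensitivity analysis.
2. **Harms:** state that women discontinued from treatment are still assessed at 30 days and six months.

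Together these reduce the bias however the per-protocol set is defined. The cost is two changes of wording, a few extra visits using procedures already planned, and slight dilution of the treatment contrast. Recruitment was still open when the article was written, and the Study amendments section gives the route.

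**Optional clarification (RF procedure):** state that an application withheld for a positive whiff test is deferred and not counted as missed. If this is adopted, time the first follow-up from the actual last application. RF women are asked to abstain from intercourse for 10 days and the FSFI looks back four weeks, so a visit at least 28 + 10 = 38 days after the last application keeps the abstinence outside the recall. A visit at 30 days would not: recall would start at day 30 - 28 = 2, leaving about 10 - 2 = 8 days of abstinence inside it, in RF women only. The cost is a later first follow-up for those few women.
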